**Methods:**

All patients admitted to the multidisciplinary neonatal and paediatric intensive care unit of a university children's hospital will be included. Patients will be allocated either to routine sepsis work up or to the intervention strategy with additional cytokine measurements. Physicians will be requested to estimate the pre-test probability of sepsis and pneumonia at initial suspicion. In the treatment arm, physicians will receive raw cytokine results, the likelihood ratio and the updated post-test probability. A high post-test probability will suggest that immediate initiation of antibiotic treatment is appropriate, whereas a low post-test probability will be supportive of watchful waiting or discontinuing prophylactic empirical therapy. Physicians may overrule the suggestions resulting from the post-test probability.

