### Intervention and controls

#### Control strategy

For patients randomized to the control arm, if the physician orders microbial cultures then they are obliged to document their best estimate of the probability that the patient has sepsis or pneumonia on two logarithmic visual-analogue scales (range 0–100%). This documentation is mandatory and must be marked on the laboratory form (Fig. 1). In the control arm blood or tracheal aspirate specimens are not analyzed; thus, physicians do not receive any information beyond routinely available data. Under the control strategy antibiotic treatment is managed according to current recommendations (cessation of therapy after 48 hours provided that blood cultures remain negative).

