#### Intervention strategy

If patients are randomized to the intervention arm, then physicians are also obliged to document their best estimate of the probability that the patient has sepsis or pneumonia, again on two logarithmic visual-analogue scales (range 0–100%). This documentation is again mandatory and must be marked on the laboratory form (Fig. 1). In the intervention arm, blood or tracheal aspirate specimens are analyzed and results are returned to the unit before 1 p.m. Physicians receive the raw cytokine values as well as the calculated likelihood ratio and the post-test probability (Fig. 2). This information is provided in addition to routinely available data. Provided that the available post-test probability indicates absence of infection, physicians are encouraged to stop antibiotic treatment. It is suggested that antimicrobial therapy be continued if the post-test probability indicates infection. It is important to note that the protocol provides only 'suggestions', and that the final decision regarding therapy is left to the discretion of the responsible clinician. This is similar to clinical routine, in which diagnostic results may suggest alterations to treatment decisions but they do not dictate treatment.

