### Randomization

The units of randomization are calendar days. Randomization is generated through pre-specified assignment of 15 working days/month as intervention days. Physicians remain blinded to the allocation roster. Thirty minutes after the deadline for delivery of samples to the laboratory (10 a.m.), physicians are informed about the randomization status (control or intervention) of the day. In this way, physicians are able to adjust their decision making while they await test results if they so wish.

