### Data collection

Routine sepsis work up includes collection of blood cultures, other microbial specimens where appropriate, and measurements of white blood cell count, including differential and plasma levels of C-reactive protein. Routine surveillance for ventilator-associated pneumonia comprises microbiological examination of the tracheal aspirate, including cultures. As described above, physicians must provide two probability estimates, one for the presence of sepsis and one for pneumonia, whenever they order a sepsis or pneumonia work up. This ensures that clinicians state their estimate before knowledge of the test result. These estimates (pre-test probabilities) are integrated with cytokine concentrations derived from likelihood ratios for sepsis or pneumonia using Bayes' theorem. The algorithms for calculating post-test probabilities are presented in Table 1. A study nurse records clinical data for both groups on the day preceding collection of culture specimens and on the following 6 days (Fig. 3). We will collect data on mortality, but this will not be included as a study outcome because of low mortality rates and the intended study size. Further data are collected from the hospital's database. This database contains all physician's reports, patient baseline data, routine laboratory results, pharmacology data, costs per patient and day of specific medications (e.g. fresh frozen plasma), and staff allocation.

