### Sample size calculation and statistical considerations

At present, in the ICU antibiotic therapy is employed in 40% of patients, which represents a decline from our original survey conducted in 1998 (up to 80% of all patients) [3]. The expected reduction in antibiotic usage is 10–25%, with a clinically relevant reduction considered to be any reduction in excess of 10%. The minimum number of days of hospitalization in each arm required to detect a 10% reduction with a type I error under 5% and a power of 80% is 2300. The expected follow up rate is in excess of 90%. Because the unit of randomization is days and not individuals, an unknown intracluster (intraday) correlation coefficient must be considered. The standard χ^2 ^statistic, which assumes independence of individuals, may not be applicable. We may be forced to acknowledge the nested nature of the data (clustered randomized controlled trial) by using test statistics based on the generalized linear mixed model [12]. To safeguard against insufficient power we believe that the sample size must be increased to 25%, leading to a required accrual of 3000 hospitalization days per arm. Given the size of the participating units, this translates to a study duration of 24 months.

All analyses will be carried out on an intention-to-treat basis. This means that any antibiotic treatment course will be allocated according to the randomization status of the day on which the decision to withhold or to continue had to be made. This requires us to perform three subgroup analyses: antibiotic prescription prevalence according to the day's randomization status; antibiotic free days following the 4 days after any microbiological work up; and antibiotic free days during the week following any initiation of antibiotics.

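### Windows opened after every work-up or antibiotic start can overlap across control and intervention days, so the same antibiotic-free days can count in both arms

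*Protocol article*

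**What the plan says.** **Unit of allocation.** The Randomization section is explicit: "The units of randomization are calendar days". The section on sample size and statistical considerations repeats that days, not individuals, are randomized. Three other places speak of patients. The Abstract (Methods) has "Patients will be allocated either to routine sepsis work up or to the intervention strategy with additional cytokine measurements", the Control strategy has "For patients randomized to the control arm, if the physician orders microbial cultures", and the Intervention strategy has "If patients are randomized to the intervention arm".

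**Analyses.** The statistical section gives each antibiotic course the status of the day on which the decision about it was due. It then lists three analyses:

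1. prescription prevalence by the status of the day;
2. "antibiotic free days following the 4 days after any microbiological work up", read here as antibiotic-free days in the four days after a work-up;
3. antibiotic-free days in the week after each start of antibiotics.

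**Repeat work-ups.** Data collection states: "Routine surveillance for ventilator-associated pneumonia comprises microbiological examination of the tracheal aspirate, including cultures". No frequency is given. No passage says how a second work-up, or a second antibiotic start, inside an open window is to be handled.

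**The concern.** Days of both kinds alternate within a patient's stay. If every work-up and every start opens its own window, one patient can have a control window and an intervention window running together. Three things follow.

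- The same antibiotic-free days are outcome data for both arms, which pulls the two means together and breaks independence between arms.
- A window classified as control can contain a cytokine result released at a later work-up, so part of the control outcome may reflect the intervention.
- Whether a later window exists can depend on the earlier allocation. For example, a course stopped early after a cytokine result can be restarted within the week and open a second window. A course that is still running cannot.

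The safeguards in the article address other matters. The sample size increase is for intraday correlation, and the Discussion foresees that learning or greater awareness may affect the control arm. Neither deals with overlapping windows in one patient.

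**Working it through.** **1. The plan's own figure.** Inputs from the statistical section: 40% antibiotic use, a 10% relative reduction (0.40 to 0.36), type I error 5% (taken as two-sided), power 80%.

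n = [1.96·√(2·0.38·0.62) + 0.842·√(0.40·0.60 + 0.36·0.64)]² / 0.04² = 2311 per arm, against the stated 2300.

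The figure reproduces. It treats each hospitalization day as independent and as belonging to one arm. It concerns antibiotic use over hospitalization days, and no power basis is given for the two window analyses.

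**2. Overlap.** Take work-ups on Monday (control) and Tuesday (intervention).

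| Window | Days |
|---|---|
| Monday, control | Tue, Wed, Thu, Fri |
| Tuesday, intervention | Wed, Thu, Fri, Sat |

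Wednesday to Friday count in both arms: 3 of 4 days. In general, two work-ups d days apart share 4 − d days (3, 2, 1 for d = 1, 2, 3). Two antibiotic starts d days apart share 7 − d days (6 down to 1 for d = 1 to 6).

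**3. Chance that a repeat falls on an intervention day.** The Randomization section assigns 15 working days per month. Assuming 30.4 calendar days and 21.7 working days per month, the share f is 15/30.4 = 0.49 of calendar days or 15/21.7 = 0.69 of working days. Assuming repeat days are allocated independently, the chance of at least one intervention day among k repeats is 1 − (1 − f)^k.

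| k | f = 0.49 | f = 0.69 |
|---|---|---|
| 1 | 0.49 | 0.69 |
| 2 | 0.74 | 0.90 |
| 3 | 0.87 | 0.97 |

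**4. What cannot be computed.** The share of control windows containing a result is r·f when a fraction r has one repeat. The documents give no r. Purely as an assumption, r = 20% with f = 0.493 gives 0.10, and r = 50% with f = 0.691 gives 0.35. This is a share of windows exposed, not a loss of effect. A result returned d days after the index leaves only the rest of the window open to change. Under the Control strategy, therapy with negative blood cultures ends after 48 hours anyway.

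**5. The other rules.** Prevalence by day's status counts each patient-day once, under that day's status. The course rule gives a course to one decision day, although it does not say which day governs when a course has several work-ups. Neither rule governs the two window analyses, whose windows are tied to each work-up and each start.

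**The case against.** **The unit is settled.** The Randomization and statistical sections both say days. The patient wording is therefore loose drafting, not a rival design. A reader might infer that a patient first worked up on a control day should remain control throughout. The Control strategy does not say so, and a patient appearing in both arms is inherent in day randomization. This part of the objection stands.

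**Overlap handling belongs in an analysis plan.** This stands only in part. An article may omit such detail, but this one fixes a rule: the windows follow each work-up or start without restriction. Applied as written, that rule allows overlap.

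**Frequent repeats are not shown.** This also stands. No surveillance frequency is given. The Pilot study section confines the trial to suspected infection, while the Objectives speak of routine surveillance. A reader might infer that physicians would re-culture because a day turned out to be control. They are blinded to the roster and cannot know the next day's status, so this is speculation.

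**The dilution is unproven.** A reader might also infer that a true 10% reduction would appear as about 7.5–9%. That takes 20–50% of control episodes having one repeat, a one-half chance of an intervention day, and the full intervention effect in every exposed control: 10% × (1 − 0.25) to 10% × (1 − 0.10). The first input is not in the documents, and the last makes the loss an upper bound for the assumed exposure. The range is not an estimate for this trial.

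**Conclusion.** The point holds for the two window analyses. As written, they let control and intervention windows overlap in one patient, let the same antibiotic-free days enter both arms, and let a control window contain a cytokine result. They also let the existence of a later window depend on earlier allocation. Crossing can occur but need not. It requires a repeat on a day of the other status, with probability about 0.49 to 0.69 for one repeat after a control day if days are allocated independently.

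The size of the resulting bias cannot be derived without a repeat-culture rate. Exposure of control windows and shared days both push toward no difference. Selection of later windows has no direction that the documents fix.

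It would go too far to say that antibiotic days are counted twice throughout the trial. The prevalence analysis by day's status does not do this, and the sample size figure is not at fault here. The patient-allocation wording needs reconciling with day randomization but does not change the design.

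**What to change.** Change the wording and the analysis only. Release of cytokine results stays tied to the day's status. Fixing an episode's arm and withholding later results would be a redesign: it would make later allocation predictable, conflict with day randomization and reach into clinical management.

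1. **Wording.** In the Abstract, Control strategy and Intervention strategy, describe work-ups on control or intervention days in place of patients randomized to an arm.
2. **Index.** For the work-up analysis, the index is a work-up with none in the preceding 4 days. For the initiation analysis, it is an antibiotic start with none in the preceding 7 days. Classify the window by the index day's status.
3. **No nesting.** Open no new window inside an existing one.
4. **Model.** Include patient as well as day as random effects. The article already foresees a generalized linear mixed model.
5. **Report.** Give the share of control-index windows in which a cytokine result was released on a later intervention day, and state that this biases toward no difference.

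A second index window in the same patient may still depend on the earlier allocation. A sensitivity analysis using each patient's first index window would show whether this matters.

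Cost: fewer windows and slightly less precision in these two analyses. No extra patients, assays or laboratory procedures are needed.

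### The third antibiotic analysis is called intention-to-treat but admits only started courses, and starting is something the test result can prevent or trigger

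*Protocol article*

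**What the plan says.** The section on sample size and statistical considerations states: "All analyses will be carried out on an intention-to-treat basis". It attributes each course to "the randomization status of the day on which the decision to withhold or to continue had to be made" and then names three analyses:

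1. "antibiotic prescription prevalence according to the day's randomization status"
2. "antibiotic free days following the 4 days after any microbiological work up"
3. "antibiotic free days during the week following any initiation of antibiotics"

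The first is counted by day and the second by work-up. Only the third requires that antibiotics were started. The three are not ranked, and the outcome section sends the reader here for details of the primary measure.

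The abstract's methods paragraph describes what the result is meant to change. On one side, "a low post-test probability will be supportive of watchful waiting or discontinuing prophylactic empirical therapy". On the other, "A high post-test probability will suggest that immediate initiation of antibiotic treatment is appropriate". The randomization section says that physicians learn the day's status half an hour after the 10 a.m. sample deadline, so that "physicians are able to adjust their decision making while they await test results if they so wish".

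**The concern.** An intention-to-treat comparison keeps every allocated unit, whatever happens after allocation. The third analysis keeps a unit only if antibiotics were begun, and the strategy can alter that event in both directions. A suspected episode in which the result leads the physician to withhold treatment is a success of the strategy, yet it leaves the intervention arm. Its counterpart on a control day stays in, typically as a short course with many antibiotic-free days. The started courses in the two arms are then different kinds of patient.

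At stake is the reading of one of three unranked antibiotic analyses. It could contradict the primary result for reasons unrelated to whether the strategy works.

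**Working it through.** **Figure in the plan.** The plan attaches no number to this analysis. Its one relevant figure, 2300 days per arm, belongs to the comparison of 40% with 36% (a 10% relative reduction). With two-sided 5% and 80% power, n = [1.960·√(2·0.38·0.62) + 0.842·√(0.40·0.60 + 0.36·0.64)]² / 0.04² ≈ 2311. This reproduces the figure and is not affected by the point made here.

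**Inputs.** The control strategy stops treatment at 48 hours if cultures stay negative, and the introduction gives 48–72 hours as usual, so a short course is 2 or 3 days. The objectives speak of stopping within 24 hours, so a curtailed course is 1 day. Only a minority of treated patients are truly infected, and no share is given. The case mix, the 7-day length for infected courses and the share of starts prevented are therefore assumptions.

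**Assumed mix, 100 suspected episodes per arm.** Control: 50 rule-out courses of 2 days, 30 courses of 7 days, 20 never started.

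- Antibiotic days: 50·2 + 30·7 = 310.
- Free days per started course: (50·5 + 30·0)/80 = 3.13.
- Free days over all episodes: (700 − 310)/100 = 3.90.

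| Assumed intervention effect | Antibiotic days | Free days per started course | Free days over all episodes |
|---|---|---|---|
| None (control) | 310 | 3.13 | 3.90 |
| 10 rule-outs prevented | 40·2 + 210 = 290 (−6%) | 40·5/70 = 2.86 | 4.10 |
| 20 rule-outs prevented | 30·2 + 210 = 270 (−13%) | 30·5/60 = 2.50 | 4.30 |
| 10 prevented, other 40 cut to 1 day | 40·1 + 210 = 250 (−19%) | 40·6/70 = 3.43 | 4.50 |
| 20 prevented, other 30 cut to 1 day | 30·1 + 210 = 240 (−23%) | 30·6/60 = 3.00 | 4.60 |
| 10 extra 2-day courses triggered | 60·2 + 210 = 330 (+6%) | 60·5/90 = 3.33 | 3.70 |

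The all-episodes column moves in the true direction in every row. The started-course column does not. It worsens under prevention alone, and it improves when extra short courses are triggered.

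**Break-even with full curtailment.** With k of the 50 rule-outs prevented and the rest cut to 1 day, set 6(50 − k)/(80 − k) = 3.125. Then 50 = 2.875k, so k = 17.4, or about 35%.

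**Range over other assumed mixes.** Take 60 started courses per 100 episodes, of which 5, 10 or 20 are true infections of 7 days, with short courses of 2 or 3 days.

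- *Prevention only* (10%, 25% or 50% of empirical starts avoided): the started-course mean falls in every case. The smallest fall is 49.5·4/54.5 − 55·4/60 = −0.03 day. The largest is 20·5/40 − 40·5/60 = −0.83 day. Antibiotic days fall by 4% to 41%.
- *Curtailment only* (half or all of the empirical courses cut to 1 day): the mean rises, from (20·5 + 20·6)/60 − 40·5/60 = +0.33 to 55·6/60 − 55·4/60 = +1.83 days.
- *Both, with full curtailment of the remainder*: the sign reverses only when the prevented share exceeds 37.5% (20 infections, 2-day courses) to 86% (5 infections, 3-day courses).

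**The case against.** The strongest reply is that the trial works mainly by stopping courses already begun. The intervention section speaks only of stopping or continuing, the objectives of discontinuing within 24 hours, and the stopping rules of shortening empirical therapy from 48 to 24 hours. Under that mechanism the analysis usually moves the right way, as the curtailment results show. This stands.

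Three further points also stand:

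- A course begun before the status is disclosed cannot depend on that day's status. The share of starts that wait for disclosure or results is not given.
- Test-triggered short courses push the measure in the opposite direction.
- The primary rate and the first two analyses count withheld courses, and the second already enters by work-up, though it refers to 4 days.

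It can also be argued that withholding, when paired with continuing, means ending an existing course. That reading is possible, but the abstract separately names watchful waiting and immediate initiation. A start can therefore depend on the result whichever way that sentence is read.

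A reader might infer that the analysis is certain to be biased against the strategy, or that the trial's main result is compromised. The documents support neither. They give no prevented share, they describe channels acting in both directions, and the primary rate does not condition on a start.

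**Conclusion.** The third analysis does not meet the intention-to-treat label given to it, because it selects on an event that allocation can change after disclosure. This follows from the protocol's own text and needs no assumed numbers.

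The consequence is conditional. If prevention of short empirical courses outweighs curtailment, a genuine saving can appear null or reversed. In the assumed mix with prevention only, the shift is 3.13 to 2.50 free days while antibiotic days fall 13%. With full curtailment of the remaining short courses, reversal needs roughly 35% to 86% of them prevented, depending on the mix. Below that level, prevention still offsets part of the gain from curtailment. Size and net direction cannot be fixed from the documents. The point is confined to one of three antibiotic analyses, and the sample size is untouched.

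**What to change.** Redefine the third analysis as antibiotic-free days in the 7 days after every episode of suspected infection. An episode is a work-up with a pre-test probability estimate, or an antibiotic prescription. Leave out routine surveillance cultures taken without suspicion, which would otherwise dilute the contrast. Analyse by the allocation of the decision day and count never-started episodes as 7 antibiotic-free days. As far as possible, settle entry and the surveillance exclusion from what was recorded before the day's status was disclosed, so that the same selection does not return through the entry rule.

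Keep duration among started courses as a descriptive result, stated not to be intention-to-treat.

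The cost is a sentence or two in the statistical section. The design section already requires an estimate for any antibiotic prescription, so few started courses should be lost. The study nurse's records cover the days around each culture, and the hospital database's pharmacology data can supply any day of the week they miss. The downside is small: the measure is no longer purely one of course duration, and it overlaps with the 4-day work-up analysis.
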